# Quantitative Data collection

Quantitative data will be collected using questionnaires translated into the local Somali language, and addressed to the primary carer of the child included in the study. A household surveillance system will be set up to collect anthropometric data that will be used to evaluate whether the intervention changes the primary and secondary outcomes listed above. Data collection will be done monthly at the household level by a team of CHW, closely supervised by Concern Nutrition Supervisors and the Study Coordinator. The questionnaires will include the data collection listed below but note that not all variables will be collected each month. Figure 4 provides a schematic to explain the data collection plan for each month of the study.

Separate household, child (0-59 month), and Mother/questionnaires will be used.

(a) Household questionnaire: The data collected will include: camp name, HH ID, data of arrival, age, sex, region of origin, date of interview, reduced coping strategies index, household food insecurity access scale (HFIAS) score, food consumption score (FCS).

(b) Child (0-59 months) questionnaire: HH ID, personal ID, vaccination status, 7 day morbidity recall, 24 hour dietary recall, mid upper arm circumference (MUAC), and nutritional oedema.

(c) Mother/carer: HH ID, personal ID, age, parity, region of origin, clan, health and nutrition knowledge, diet diversity score

Those identified as malnourished or sick will be referred to local nutrition or health centres for treatment.

Figure 3 Schematic of data collection schedule

Full data collection will be undertaken at the time points marked in blue while a reduced questionnaire will be used at the other monthly data collection time points. This will enable effective monitoring of changes during the intervention period while reducing the burden on the participants and data collection team.

[figure not shown]

In the Somalia context, membership of clan and sub-clans is an important cultural and political factor. Clan membership is thought to influence vulnerability during crises and we will explore this hypothesis using the data we will collect on clan membership from all participants.

Verbal Autopsies will be conducted to determine the cause of death of any children who die during the study. When deaths are recorded by the study surveillance system, an interview team will conduct a household visit after an appropriate suitable period has elapsed. VA is the process of interviewing close caregivers of the deceased about symptoms and the circumstances of death. It has been widely used in research and over the past decade the WHO and partners have developed shorter, standardized survey tools and automated interpretation methods which can overcome barriers to their use in humanitarian contexts. It is now possible to administer a VA within about 20 minutes and immediately identify probable causes of death.

Trained fieldworkers will visit the next-of-kin in their residence within 4-8 weeks of notification of a death. Fieldworkers will administer the WHO 2016 VA questionnaire.[17] This questionnaire is comprised of a series of yes/no/don’t know questions relating to the signs, symptoms, circumstances and care-seeking (collectively called ‘indicators’) leading to death. Interviews will be conducted in Somali and data will be captured using a mobile phone with automated skip patterns and internal data checks.

VA data will be uploaded to a local database daily and run through InterVA software (www.interva.net). For every death, InterVA will identify multiple possible causes of death, each with an assigned likelihood. When aggregated, with individual deaths being split between multiple causes according to their likelihood weighting, these data give a representation of the cause distribution at the population level. The method has been applied in numerous settings and compares favourably to alternative means of identifying cause of death from VA with the added advantages of better timeliness, lower cost, and improved reliability.

# Qualitative data collection

The study will have a strong qualitative component. The qualitative data will be used to help inform the design of the intervention during the piloting stage (see above) and to understand the context of the study, the fidelity of the intervention implementation, and any unexpected outcomes of the interventions. Data will be collected using Interviews, focus group discussions (FDG), and observation notes. FGD and interviews will be recorded using handheld tape recorders. The qualitative data collection will be undertaken by a team of two data collectors, who have been trained in qualitative methods, and a supervisor.

Data collection will be carried out by mixed gender teams and qualitative research will be conducted by researchers of the appropriate gender to engender trust and openness in the different respondent groups. CHWs will be trained on culturally sensitive mobilization skills that help them understand how to work in communities during mobilization, research, and intervention activities. The time taken to conduct interviews will be minimized to reduce the opportunity costs for the household, and minimize the use of the respondent’s time. CHWs will also ensure all children are included in the surveillance system independent of whether they have an impairment (as children with disability are sometimes missed).

# Data Management

Data will, preferably, be collected on mobile digital devices, such as Samsung smart phones, using Open Data Kit (ODK) based software. Data will be uploaded to Ona Data servers as and when network connections are available. The uploaded data will be downloaded in standard.csv file format and imported into Stata v14 statistical analysis software. Relational databases will be constructed and data cleaning performed using standard techniques. Anthropometric indices will be calculated using WHO macros.

# Data Analysis

Data analysis will be conducted using Stata v14 software. Difference-in-difference analysis will be used to describe differences between arms in hypothesised mediating variables such as health and nutrition knowledge. Linear and logistic regression models will be used to test the main hypotheses while adjusting for covariates that are found to be associated with outcome measures and may act as potential confounders on the causal pathway.

Primary analysis will be conducted based on intention to treat. Secondary analysis will use monitoring and adherence data to assess for any dose response effect associated with the BCC or cash interventions.

Qualitative data will be transcribed in Somali, translated into English, and analysed using the framework method for thematic analysis. Analysis will be conducted using Nvivo qualitative data analysis Software (QSR International Pty Ltd. 2012. Version 11).

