# Study Design

The research will take place in 20 IDP camps in the Afgooye Corridor, which are expected to contain an average population size of 65 children (aged 0-59 mo.) per camp. A 2x2 factorial design will be used with cluster randomization. A cluster will comprise one IDP camp. The study design is illustrated below.

Table 2 Study Design Summary

|  | Unconditional  Cash Transfer | Conditional  Cash Transfer |
| --- | --- | --- |
| No mHealth BCC | 5 camps | 5 camps |
| mHealth BCC | 5 camps | 5 camps |

All households within the 20 selected IDP camps will be invited to participate in the study so it is anticipated that a total of 1,300 children will be recruited. Measurements will be taken at monthly household visits, which will be done by community health workers, and continue during the course of the intervention. Children who exceed the age of 59 mo. during the course of the study will continue to be followed until the end of the follow-up period. Any new households that arrive in the IDP camps after the household recruitment has finished will not be invited to enrol.

Participant exclusion criteria:

1. Children with a disability that prevents taking weight or height measures

2. Children with a medical condition that prevents them eating a normal diet

3. Children confined to bed due to illness

4. Children living in a household in which the mother/carer is unable to respond to questions due to a speech or hearing impairment

This study design will allow us to address 2 main hypotheses:

(1) Humanitarian cash transfer conditionality improves health service utilization, increases vaccination coverage by 20%, and reduces morbidity in children aged 6-59 months.

This hypothesis will be tested by comparing the 10 clusters receiving unconditional cash with the 10 clusters receiving conditional cash transfers.

(2) A mHealth mobile phone BCC messaging intervention, linked to cash transfers, will improve health knowledge and nutrition related behaviours in a complex emergency context.

This hypothesis will be tested by comparing the 10 clusters who receive the mHealth intervention with those that do not. We will also test the secondary hypothesis that a combined conditional cash transfers and mHealth mobile phone BCC messaging intervention reduces the risk of acute malnutrition compared to those receiving unconditional cash transfers or no mHealth intervention.

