# Outcome measures

- Measles vaccination coverage - % of children 9-<59 months of age who received measles vaccine
- EPI vaccination coverage - % of children 0-<59 months of age who received all vaccines required by the national vaccination protocols
- Child diet diversity score of children 6-<24 months of age
- Parental/caretakers knowledge of BCC health and nutrition topics

The secondary outcomes of interest are:

- Incidence of acute malnutrition - MUAC<12.5 cm or oedema among children 6-59 months
- Incidence of mortality among children 6-59 months
- Exclusive breastfeeding prevalence - % of infants 0-5 months who were exclusively breastfed during the last 24 hours ​
- Incidence of child morbidity
- Causes of death ascertained by Verbal Autopsy

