# Sample Size Calculations

The sample size available to test for differences in vaccination coverage (hypothesis 1) was assessed using clustersampsi in Stata v14. Based on current measles vaccination coverage data, collected during the REFANI trial, we expect to see a baseline coverage of around 64%. With 10 clusters (camps) per arm and an average population of 65 children (aged 0-59 months) per cluster, and allowing for an alpha risk of 0.05, a power of 0.8, and an ICC of 0.06, we will be able to detect a minimum increase of 18 percentage points. This minimum detectable difference lies below our hypothesized effect size of 20 percentage points.

To calculate a sample size to test hypothesis 2 - the effect of mHealth messaging on health knowledge and nutrition behaviours - we assumed that there will be no interaction between the mHealth and conditionality interventions. Under this assumption we assessed the utility of the available sample size to detect a difference in children’s diet diversity score between the clusters receiving the mHealth intervention and those that won’t. Based on data from the REFANI study we expect to see a baseline child diet diversity score of 3 and a SD of 2. With 10 clusters (camps) per arm and an average population of 65 children (aged 0-59 months) per cluster, and allowing for an alpha risk of 0.05, a power of 0.8, and an ICC of 0.01, we will be able to detect a minimum increase of 0.42 in the diet diversity score. These calculations confirm that the study design is well powered to detect differences in our primary outcomes.

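### Caregiver knowledge is a primary outcome whose only named analysis is a descriptive difference-in-difference, and main hypothesis 1 names service utilisation without an outcome or data item for it

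*Protocol*

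**What the plan says.** **Knowledge as an outcome.** Outcome measures opens with an unlabelled list of four: measles coverage, full EPI coverage, child diet diversity, and "Parental/caretakers knowledge of BCC health and nutrition topics". A second list then begins with "The secondary outcomes of interest are". Two later sections show that the first list is meant as primary. Quantitative Data collection says the data will be used to "evaluate whether the intervention changes the primary and secondary outcomes listed above", and Sample Size Calculations ends with "These calculations confirm that the study design is well powered to detect differences in our primary outcomes".

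**Knowledge as a hypothesis target.** Under Study Design, main hypothesis 2 states that the mHealth messaging "will improve health knowledge and nutrition related behaviours in a complex emergency context". It is to be tested by comparing the 10 messaging camps with the 10 others.

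**Knowledge as a mediator.** Data Analysis states: "Difference-in-difference analysis will be used to describe differences between arms in hypothesised mediating variables such as health and nutrition knowledge". The following sentence assigns linear and logistic regression to the tests of the main hypotheses, with adjustment for covariates found to be associated with the outcomes.

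**Utilisation.** Main hypothesis 1 reads: "Humanitarian cash transfer conditionality improves health service utilization, increases vaccination coverage by 20%, and reduces morbidity in children aged 6-59 months". The substantive child items in Quantitative Data collection are "vaccination status, 7 day morbidity recall, 24 hour dietary recall, mid upper arm circumference (MUAC), and nutritional oedema". The household and mother/carer questionnaires, as listed, contain nothing on clinic visits.

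**The concern.** A primary outcome needs one analysis that decides it. Knowledge has a descriptive one under its own name and an inferential one only if the reader counts it among the main hypotheses. If the two disagree, the protocol gives no ground for preferring either, and the choice could be made after the results are seen.

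The named method is also the weaker one. Under randomisation, baseline knowledge differs between arms only by chance. Subtracting it in full over-corrects whenever baseline and endline are imperfectly correlated. With 10 camps per side of each comparison, there is little precision to give away.

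Main hypothesis 1 has a parallel gap. One of its three components has no definition, so whatever is later reported as utilisation would be chosen without a prior commitment.

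**Working it through.** No figure in the protocol attaches to this point, so there is none to reproduce. The sample size section has calculations for measles coverage and diet diversity, and none for knowledge or utilisation.

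**1. Role of knowledge, place by place**

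| Section | Role given to knowledge |
| --- | --- |
| Outcome measures | Fourth item of the list that precedes the secondary outcomes |
| Study Design | Target of main hypothesis 2 |
| Data Analysis, difference-in-difference sentence | Mediator, to be described |
| Data Analysis, next sentence | Not named; covered only if read as part of hypothesis 2 |

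The regression sentence does not mention the baseline value of the outcome. Even on the reading that covers knowledge, it does not commit to baseline adjustment.

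**2. Precision**

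Take an outcome with variance 1 at baseline and at endline and correlation r between them. The variance of the treatment contrast, up to a common factor, is:

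- endline only: 1
- difference-in-difference (change score): 2(1 − r)
- endline adjusted for baseline: 1 − r²

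The ratio of adjusted to difference-in-difference is (1 − r²) / [2(1 − r)] = (1 + r)/2.

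| Assumed r | Endline only | Difference-in-difference | Baseline-adjusted | Variance ratio (1+r)/2 | Standard-error ratio (square root) |
| --- | --- | --- | --- | --- | --- |
| 0.3 | 1 | 1.40 | 0.91 | 0.65 | 0.81 |
| 0.5 | 1 | 1.00 | 0.75 | 0.75 | 0.87 |
| 0.7 | 1 | 0.60 | 0.51 | 0.85 | 0.92 |

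Confidence intervals would therefore be roughly 19%, 13% and 8% narrower with baseline adjustment. Since 2(1 − r) exceeds 1 when r is below 0.5, difference-in-difference is then worse than ignoring baseline altogether.

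The values of r are assumptions. Because camps are randomised, the relevant r mixes the correlation of camp means over time with that of individual caregivers, and it may differ from the individual-level value. The ratio stays below 1 for any r below 1. Estimating the slope takes back a small part of the gain.

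**3. Utilisation**

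- Outcome measures: no utilisation outcome in either list.
- Quantitative Data collection: no attendance or care-seeking item for living children. The care-seeking questions in the verbal autopsy concern deaths only.
- Cash Transfer Intervention: community health workers check child health cards monthly for vaccination, vitamin A and deworming. This records part of service use.
- Same section: a clinic visit is verified at registration for conditional cash, while unconditional households are not asked for a card at that point. Whether the monthly checks cover the unconditional arms is not explicit. A measure built from cards could therefore be ascertained differently by arm.

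Morbidity is also in hypothesis 1 and is listed as secondary, but it is collected. That is a matter of labelling.

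**The case against.** **A variable may be both outcome and mediator.** Knowledge can be an end point of hypothesis 2 and also a step towards less malnutrition, and the regression sentence can be read to include it. This stands. A reader might infer that knowledge is never formally tested; the protocol does not show that. What remains is that two analyses are available and neither is named as decisive.

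**The choice of model is a preference and may sit in an SAP.** Both methods are valid under randomisation, and model detail is often left to the SAP. But here the protocol itself names the method for this variable, and it is the less precise one. That r is assumed is a fair criticism. It affects the size of the gain, not its direction.

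**Utilisation is partly captured.** This also stands. A reader might infer that utilisation is not measured and that part of hypothesis 1 cannot be tested. Vaccination status and the card checks make that too strong. The supported statement is that no outcome and no clinic-attendance item are defined.

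**Error rates.** A reader might go on to infer that four primary outcomes inflate the false-positive rate. The documents do not support this. An alpha of 0.05 appears only in the two sample size calculations, no rule says that any single success confirms a hypothesis, and hypothesis 1 joins its parts with *and*. How multiplicity is handled is commonly left to an SAP.

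**Wider remedies.** It would be tempting to let diet diversity alone decide hypothesis 2 because it has a calculation. That calculation counts 65 children aged 0-59 months per camp, while the score is defined for ages 6 to under 24 months. Nor can child-level baseline adjustment be prescribed for every outcome: with 9 months of transfers, some children in that age range at the end would have been too young for the score at the start.

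**Conclusion.** The concern holds in two limited parts.

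First, knowledge is a primary outcome by implication and a target of main hypothesis 2, but its one explicitly named analysis is descriptive and less precise than a simple alternative. The loss is moderate: baseline adjustment would have 0.65 to 0.85 of the variance for r from 0.3 to 0.7. This assumes equal variances at the two times, the same caregivers measured at both, and an r that the protocol does not supply.

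Second, main hypothesis 1 names utilisation with nothing defined to measure it. This has no numerical size. It leaves one component of a main hypothesis open to definition after the fact.

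Neither part invalidates the design. Both are worth correcting because the correction is nearly free.

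**What to change.** **Data Analysis.** State that caregiver knowledge is tested as a hypothesis 2 outcome, by regression of endline knowledge on allocation and baseline knowledge, accounting for camp. Keep any mediator analysis of knowledge, including a difference-in-difference description, as secondary. Difference-in-difference already presupposes a baseline measurement, so no new data are needed.

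**Outcome measures.** Label the first list as primary, so that the role of knowledge no longer rests on inference.

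**Study Design and Quantitative Data collection.** Either remove utilisation from main hypothesis 1, or add one clinic-visit item to the existing child questionnaire, asked in the same words and at the same visits in all four arms, and list the corresponding outcome.

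**Cost.** Wording changes and at most one questionnaire item. Sample size, randomisation and visit schedule are unaffected.

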## Cash Transfer Intervention

Cash will be provided to households either as an unconditional or conditional cash transfer. All groups will receive cash transfers due to ethical reasons, as all households are considered to be suffering from extreme poverty and to be highly vulnerable. Randomization will be done at the cluster (camp) level. Households living in the selected camps will be listed and registered by the Concern cash distribution team.

The cash distribution will be done electronically each month and the specified amount will be sent to the registered SIM card of the beneficiary in US$. The cash transfers will be implemented by Hormuud Telecom via their EVC Plus money transfer service.[[2]](#footnote-3) Once the beneficiaries receive the cash transfer they can then use it to purchase items electronically or exchange for physical cash at a wide range of local shops. If they experience problems with use of the cash transfer they can contact the local Hormuud Telecom office for assistance. Problems can also be reported to the Concern beneficiary help line.

Cash transfers will follow the standard amounts set by the Somalia Cash Working Group based on a percentage of the Monthly Expenditure Basket (MEB). The cash transfers will be provided for 9 months. For the first 3-6 months the transfer amount provided will be that given during a humanitarian cash transfer programme; for the following 6 months the amount provided will be aligned with that given by social safety net (welfare) programmes.

The conditional cash transfer will require households with children, aged 0-59 months, to have first attended the local health clinic where they will receive a health screening, any necessary vaccinations, deworming, and vitamin A supplementation as required; and they will be issued with a child health record card. All the study camps have similar access to local health clinics. The health clinic visit will be verified by asking for the child health record cards during registration of the household for cash transfers.

Checks of child health card will be carried out monthly during the monthly monitoring household visits by CHWs. The check will monitor whether all children in the household 0-59 months are up to date on routine vaccination, vitamin A supplementation, and deworming.

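### The regressions named for the main hypotheses give no account of camp, the unit of randomisation; if camp were ignored, type I error would be about 37% for measles coverage and up to about 13% for diet diversity

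*Protocol*

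**What the plan says.** **Randomisation.** The protocol allocates camps, not children. Under Cash Transfer Intervention: "Randomization will be done at the cluster (camp) level". Under Study Design: "A 2x2 factorial design will be used with cluster randomization. A cluster will comprise one IDP camp". There are 20 camps, five in each of the four cells.

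**Comparisons.** Study Design describes the test of hypothesis 1 as "comparing the 10 clusters receiving unconditional cash with the 10 clusters receiving conditional cash transfers" and that of hypothesis 2 as "comparing the 10 clusters who receive the mHealth intervention with those that do not".

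**Sample size.** Sample Size Calculations starts from "With 10 clusters (camps) per arm and an average population of 65 children (aged 0-59 months) per cluster". For measles coverage it uses "a power of 0.8, and an ICC of 0.06"; for diet diversity the same power with an ICC of 0.01.

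**Analysis.** The Data Analysis section is the only text on quantitative analysis. It says that "Linear and logistic regression models will be used to test the main hypotheses". It also gives a rule for adjustment, by which a covariate enters if it relates to the outcome and might confound the effect, and it makes the primary analysis by intention to treat. Nowhere does it mention camp, cluster, a random effect, generalised estimating equations, robust standard errors or camp-level summaries.

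**The concern.** Children in one camp share a clinic, health workers and living conditions, so their outcomes are correlated. The protocol accepts this when it sizes the trial. A linear or logistic regression on children with no allowance for camp treats 650 children per side as 650 independent observations, although only 10 units per side were randomised. Its standard errors are then too small and its p-values too low.

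The Data Analysis section goes beyond a placeholder: it names the models for the main hypotheses and a rule for choosing covariates. Taken in its ordinary sense it describes regression on individual children, which does not fit the design or the sample size. At stake is whether a significant effect of conditionality on vaccination coverage could be believed.

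**Working it through.** **Inputs from the protocol.** k = 10 camps per side; m = 65 children per camp; ICC 0.06 (coverage) and 0.01 (diet diversity); alpha 0.05; power 0.80; baseline coverage 64%; diet score SD 2.

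**Assumptions.** Alpha is two-sided (the protocol does not say), camps are of equal size, and each child contributes one record.

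**Step 1. Design effect,** DE = 1 + (m − 1) × ICC; effective n per side = 650/DE.

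- Coverage: 1 + 64 × 0.06 = 4.84; 650/4.84 = 134.3.
- Diet diversity: 1 + 64 × 0.01 = 1.64; 650/1.64 = 396.3.

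**Step 2. The plan's own figures.** Detectable difference = (t at 0.975 + t at 0.80, both on 18 df) × SE, where 18 = 20 camps − 2.

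- Diet diversity: SE = √(2 × 2²/396.3) = 0.142; (2.101 + 0.862) × 0.142 = 0.421. The stated 0.42 is reproduced. With normal quantiles it would be 0.398; with camps ignored, 0.31. The stated figure thus presupposes inference at camp level.
- Coverage: the same method with unpooled binomial variance gives an increase of 16.0 percentage points; the protocol states 18. The figure is not reproduced exactly, and it errs on the cautious side. With camps ignored it would be 7.3 points, so the stated figure also clearly allows for clustering. The gap between 16 and 18 does not affect this point.

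**Step 3. Type I error if camp is ignored.** The standard error is too small by a factor of √DE, so the actual two-sided error is 2 × [1 − Φ(1.96/√DE)].

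| Outcome | Children per camp | DE | √DE | Type I error |
|---|---|---|---|---|
| Measles coverage | 65 (protocol) | 4.84 | 2.20 | 37.3% |
| Measles coverage | 55 (assumed) | 4.24 | 2.06 | 34.1% |
| Measles coverage | 50 (assumed) | 3.94 | 1.98 | 32.3% |
| Diet diversity | 65 (protocol) | 1.64 | 1.28 | 12.6% |
| Diet diversity | 30 (assumed) | 1.29 | 1.14 | 8.4% |
| Diet diversity | 20 (assumed) | 1.19 | 1.09 | 7.2% |

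The assumed rows are there because Outcome measures restricts coverage to ages 9 to under 59 months and diet diversity to ages 6 to under 24 months, while the 65 counts all children aged 0-59 months. The protocol gives no counts by age band.

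**Step 4. Simulation.** In 40,000 null trials of 10 against 10 camps with 65 children each, the test ignoring camp rejected in 37.7% for coverage (beta-binomial, 64%, ICC 0.06) and 12.8% for diet diversity (normal camp effect, ICC 0.01). A t test on camp proportions from the same coverage data rejected in 5.1%.

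**The case against.** The strongest reply is that the Data Analysis section is silent and does not rule anything out. Linear and logistic regression can be fitted with random effects, estimating equations or cluster-robust errors. Study Design frames both tests as clusters against clusters, the sample size comes from a routine for cluster trials, and the details may stand in a statistical analysis plan that is not shown. This is right as far as it goes. A reader might infer that the protocol intends to analyse children as if they had been individually randomised; the documents do not say so, and every error rate above is conditional on camp being ignored.

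Three further inferences should also be resisted:

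- **The other randomised factor.** Comparing 10 camps with 10 does not invalidate the test by leaving out the second factor. With five camps per cell the comparison is balanced, so leaving it out costs precision, not validity. Nor does the protocol say that it will be left out.
- **Repeated records.** The protocol does not say that monthly records will be stacked in one model. It says that not every variable is collected each month, and the schedule figure is not shown.
- **Diet diversity.** The 37% does not carry over to this outcome. With a plausible number of eligible children the error is only modestly above 5%.

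What the objection does not remove is the mismatch. The section chose to name the models that test the main hypotheses and omitted the one feature on which their validity depends. Software, covariate coding and diagnostics can wait for an analysis plan. A named primary test that, followed literally, does not respect the unit of randomisation should be corrected where it is named.

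**Conclusion.** The point holds in conditional form. The protocol names regressions for its main hypotheses without any account of camp, although allocation is by camp and both stated detectable differences allow for clustering. If the models were run as written with camp ignored, two-sided type I error would be about 37% for measles coverage at 65 children per camp (32 to 34% with an assumed 50 to 55 eligible) and about 13% for diet diversity at 65 per camp (7 to 8% with an assumed 20 to 30). For coverage the problem is serious: roughly one null trial in three would yield a false claim. The figures rest on the protocol's own ICCs, and they would move if the true correlations differ.

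**What to change.** Add one sentence to Data Analysis: all models for the main hypotheses account for camp as the unit of randomisation, through a random intercept for camp or an analysis of camp-level summaries, with small-sample degrees of freedom suited to 20 camps. The small-sample part should be explicit, because uncorrected robust errors or normal-based tests tend to reject too often with so few clusters.

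Putting both randomised factors in the same model (20 − 3 = 17 camp-level df) is an optional gain in precision and not needed for validity.

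The cost is wider confidence intervals than under an analysis that ignores camp. At 65 children per camp the standard error grows by a factor of 2.2 for coverage and 1.28 for diet diversity. Those wider intervals are the ones on which the sample size already rests, so no planned power is lost. Neither the interventions nor the data collection change.
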